## Abstract

**Background:**

Chronic Obstructive Pulmonary Disease (COPD) is a major cause of morbidity and mortality. Effective self-management support interventions are needed to improve the health and functional status of people with COPD or at risk for COPD. Computer-tailored technology could be an effective way to provide this support.

**Methods/Design:**

This paper presents the protocol of a randomised controlled trial testing the effectiveness of a web-based, computer-tailored self-management intervention to change health behaviours of people with or at risk for COPD. An intervention group will be compared to a usual care control group, in which the intervention group will receive a web-based, computer-tailored self-management intervention. Participants will be recruited from an online panel and through general practices. Outcomes will be measured at baseline and at 6 months. The primary outcomes will be smoking behaviour, measuring the 7-day point prevalence abstinence and physical activity, measured in minutes. Secondary outcomes will include dyspnoea score, quality of life, stages of change, intention to change behaviour and alternative smoking behaviour measures, including current smoking behaviour, 24-hour point prevalence abstinence, prolonged abstinence, continued abstinence and number of quit attempts.

**Discussion:**

To the best of our knowledge, this will be the first randomised controlled trial to test the effectiveness of a web-based, computer-tailored self-management intervention for people with or at risk for COPD. The results will be important to explore the possible benefits of computer-tailored interventions for the self-management of people with or at risk for COPD and potentially other chronic health conditions.

**Dutch trial register:**

NTR3421

## Background

Chronic Obstructive Pulmonary Disease (COPD) is a leading cause of morbidity and mortality, causing a major public health problem [1]. The disease is characterized by a progressive decline in lung function, leading to a deteriorating health status and quality of life [1]. COPD is not curable, but self-management and behaviour modification can delay further decline of health status [2].

The growing burden of COPD highlights the need for effective self-management interventions. However, only a limited number of studies have examined the effectiveness of self-management interventions and mostly in small samples [3]. These self-management interventions tend to focus on patient education. However, there is a trend to broaden this approach through personal counselling with a health care provider in order to give patients information that is relevant to their circumstances [3]. Another trend in health promotion interventions includes the use of information and communication technology, also referred to as e-Health [4].

E-Health interventions have expanded immensely during the past decade focusing on disease management and prevention [4]. Multiple e-Health interventions have been developed for COPD patients [5-7]. E-Health interventions can provide patients with health promotion information available at any time, in their own home [8]. To individualize e-Health interventions, developers may use computer-tailored technology. A computer-tailored e-Health application provides personally relevant feedback, by tailoring information to the individual needs and characteristics of the person [9], which results in increased attention, appreciation, and processing of information [10,11]. Over the years multiple variations of tailoring programs have been developed and this intervention technique has shown its potential to effectively support health behaviour change [12-14], for example smoking cessation, physical activity and interventions targeting multiple behaviours [11,15,16]. Computer-tailoring has the ability to reach large audiences at a relatively low cost [17] and tailored health promotion information is found to be more cost-effective compared to usual care [18] and motivational interviewing [19]. However, to our knowledge this technique has not been used to promote self-management of COPD patients.

In the MasterYourBreath (AdemDeBaas in Dutch) project we developed a computer-tailored self-management intervention for COPD patients. We evaluated the usability of the prototype [20] and conducted a pilot study to assess the feasibility of integrating the self-management intervention into primary care. The goal of the current study is to test the effectiveness of a web-based, computer-tailored self-management intervention for people at risk for or with COPD. This paper describes the study protocol.

## Methods

### Study design

This is a two-arm randomised controlled trial, comparing a web-based, computer-tailored self-management intervention with usual care. The study contains a design with a baseline measurement and a follow-up measurement after 6 months. We hypothesise that participants receiving a web-based, computer-tailored self-management intervention will achieve higher smoking cessation rates and obtain higher levels of physical activity compared to the control group. Moreover, we hypothesise that the intervention group will move along the stages of change continuum, have an increased intention to change their behaviour, decrease their level of disability and obtain a better COPD-related quality of life, compared to the control group. We will carry out a process evaluation in addition to this effect evaluation. The study was approved by the Medical Ethical Committee of Maastricht University Medical Centre (METC 12-4-033).

### Effect evaluation

#### Recruitment

Adults between 40 and 70 years of age, who are proficient in Dutch, have access to a computer with internet access, have basic computer skills and are diagnosed with COPD or are at moderate or high risk for COPD, are eligible for participation. The Respiratory Health Screening Questionnaire (RHSQ) [21] is used to determine whether a person has a moderate or high risk for COPD. Participants are recruited using two methods, i.e. from an existing Dutch online panel assembled by the company Flycatcher (http://www.flycatcher.eu) and from 5 general practices. Flycatcher is an institute for online research certified by the International Organization for Standardization (ISO). The total online panel is a representative sample of Dutch internet users. All active members of the online panel between 40 and 70 years of age will be invited. In case of more than one person per home address, one individual will be randomly selected and invited. Subsequently, members complete the RHSQ questionnaire to be screened for eligibility. Based on Dutch literature, we estimate that 31% of the people between 40 and 70 years old have COPD or a moderate or high risk of having COPD [22]. Members of the online panel receive a small incentive after participating in a certain number of research projects. The 5 general practices were recruited for another ongoing project in which patients are screened for COPD by their general practitioner using the RHSQ. This project examines the implementation of the RHSQ in primary care and does not aim to improve the self-management of participants. Eligible patients will be sent an invitation letter by mail for the MasterYourBreath study. All participants receive an online study information letter and have to complete an online informed consent form by checking a check box, before entering the study.

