#### Randomisation

Participants will be randomly allocated to intervention and control groups after filling out the baseline questionnaire. Randomization will be stratified by method of recruitment (online or through general practice) and participants are randomised within each stratum using a permuted block design with a random block size varying from 4 to 20. This approach helps us achieve balanced and evenly distributed samples in both groups following different recruitment strategies. A researcher who is not directly involved in other aspects of the study will perform the randomisation using PROC PLAN in Statistical Analysis System v9.1 software (SAS Institute, Cary, NC). Figure 1 shows an overview of the recruitment and randomisation process.

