#### Website

The behaviour change modules are embedded in a website, which can be accessed through a personal account. To keep the length of feedback messages as short as possible, the messages refer to background information and tools available via the website. The website contains background information about the MasterYourBreath project, COPD, risk for COPD, smoking and physical activity using written information, illustrations, videos and hyperlinks to other informative websites. In addition, videos of exercises that can be done at home are also included. New content will be added to the website once a month. This includes an interview with a COPD patient about coping with smoking and physical activity in her daily life and stories based on behavioural journalism to prompt participants to visit the behaviour change modules. Behavioural journalism promotes behaviour change by presenting peer modelling for cognitive processes that result in behaviour change [40]. Problems and reasons for participants choosing not to use the intervention that are communicated to the research team are leveraged to create the behavioural journalism stories in order to encourage the use of the behaviour change modules.

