## Discussion

This paper presents the design of a randomised controlled trial, testing the effectiveness of a computer-tailored intervention on the self-management of people with or at risk for COPD. To our knowledge, only limited research has been conducted to evaluate self-management interventions for COPD patients [3] and none of these studies used computer-tailored technology. The results of this study explore the potential benefit of using computer-tailored technology to improve self-management related health behaviours of people at risk for COPD, in addition to those with COPD.

Individuals at risk for COPD are less likely to be offered a self-management intervention by a health care provider, but they can be reached relatively easily through the internet and health behaviour change can be promoted. We also expect that including people at risk for COPD and recruiting some of the participants online increases the likelihood of assuring adequate power.

The choice for a hybrid sample of participants recruited by two methods (online panel and general practice) was made after considering the results of the pilot study (unpublished observations). In the pilot study participants were recruited by a primary care practice nurse during a yearly consultation for routine monitoring of their chronic condition. This recruitment strategy resulted in an insufficient number of participants. Not all eligible patients were invited by the nurses and many patients declined participation. We concluded that it is not feasible to recruit 446 participants per arm using this approach. Therefore, we choose to recruit participants from an online panel and through general practices by sending an invitation letter to every eligible patient.

A possible threat to this study is that large numbers of participants might not use or discontinue to use the intervention, which is common in e-Health interventions [53]. If a large percentage of participants opt not to use the intervention, an intention to treat analysis could underestimate the intervention effect [54]. For this reason we will conduct a per-protocol analysis following an intention to treat analysis.

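### The one-person-per-address rule is stated for the online panel only, so two practice patients in one home can be randomised to opposite arms; the likely effect is small

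*Protocol article*

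**What the plan says.** The Recruitment section describes two routes.

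- **Online panel.** "All active members of the online panel between 40 and 70 years of age will be invited". The address rule comes next: "In case of more than one person per home address, one individual will be randomly selected and invited". The sentence after it still concerns the panel: "Subsequently, members complete the RHSQ questionnaire to be screened for eligibility".
- **Five general practices.** "Eligible patients will be sent an invitation letter by mail for the MasterYourBreath study". The Discussion repeats that recruitment runs "through general practices by sending an invitation letter to every eligible patient". Neither place limits the number of patients per address.

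Under Randomisation, "participants are randomised within each stratum using a permuted block design with a random block size varying from 4 to 20". The strata are the two recruitment routes, the unit is the individual, and nothing keeps members of a household in the same arm.

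The intervention is a website "which can be accessed through a personal account". The section on prompts adds that e-mailed links open it without a login. The social influence component of the behaviour change modules gives the participant feedback on how a partner, among others, influences him or her, and on how he or she influences others.

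**The concern.** The sponsor saw a reason to admit only one person per home by one route but states no such safeguard for the other. Partners aged 40 to 70 may well be registered at the same practice. If both are eligible and consent, individual randomisation splits about half of such couples. The control partner may then see the site, hear its advice second-hand, or be drawn into a quit attempt or activity plan.

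Exposure of this kind raises the control result and pulls the comparison towards no effect. It falls on the practice stratum, which the Analysis section allows to be analysed separately if the two recruitment groups differ at baseline. Intention-to-treat analysis cannot remove it. Nor can the per-protocol analysis, whose only stated condition is completing an intervention component.

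**Working it through.** **1. Scope of the rule.** The address sentence stands between two sentences about panel members, so it governs the panel. The practice sentences carry no limit, and the Discussion's wording is all-inclusive. Individual randomisation then permits split households.

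**2. The plan's own figures** (Sample size calculation: 20% against 10% abstinence, 80% power, significance level 0.05 taken as two-sided, 49.2% smokers).
- Two proportions without continuity correction: n = [1.96·√(2·0.15·0.85) + 0.842·√(0.20·0.80 + 0.10·0.90)]² / 0.10² = 199 smokers per arm.
- With continuity correction: 219 smokers per arm. 219 / 0.492 = 445.1, rounded up to **446**, as stated.
- Physical activity: 2·26.63²·(1.96 + 0.842)² / 10² = 111.3, rounded up to **112**, as stated.

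**3. Share of practice controls exposed** (assumed, except the 31%, which is the article's estimate for people aged 40 to 70). Share with a co-enrolled partner = P(partner at same practice) × P(partner eligible) × P(partner joins). Half of these couples are split.

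| Case | Product | Co-enrolled | Practice controls exposed |
|---|---|---|---|
| Low | 0.6 × 0.31 × 0.3 | 5.6% | 2.8% |
| Central | 0.7 × 0.31 × 0.5 | 10.9% | 5.4% |
| High | 0.8 × 0.50 × 0.8 | 32% | 16% |

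If every exposed control gained the full effect, the 10-point difference within the practice stratum would become 9.7, 9.5 or 8.4 points.

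**4. Whole-trial power for smoking**, with 219 smokers per arm and an assumed 30% practice share. Exposed share f = 0.30 × (practice controls exposed); diluted control rate pc = 0.10 + 0.10·f.
- Wald test on the log odds ratio: power = Φ(δ/SE − 1.96), with δ = ln(0.20/0.80) − ln[pc/(1 − pc)] and SE² = 1/(219·0.20·0.80) + 1/[219·pc·(1 − pc)].
- Two-proportion z-test, without continuity correction.

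| Case | f | Power, Wald | Power, z-test |
|---|---|---|---|
| No exposure | 0 | 82.1% | 83.7% |
| Low | 0.8% | 81.4% | 82.9% |
| Central | 1.6% | 80.8% | 82.3% |
| High | 4.8% | 77.9% | 79.4% |

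In the central case about 7 of 446 controls are exposed (446 × 0.016), and power falls by 1.4 points on either test.

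**5. Discount for smoking.** The smoking module would normally reach a control smoker only through a partner who also smokes. Multiplying f by 0.492, and assuming that partners' smoking is independent, gives 81.5% or 83.0% in the central case and 80.1% or 81.6% in the high case.

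**6. Physical activity.** With 446 per arm against 112 needed, power exceeds 99.9% with no exposure and also in the high case.

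**The case against.** The strongest case against is that a condensed article need not describe how a practice mailing list is de-duplicated, and that the Discussion remark about inviting everyone is there to contrast letters with the pilot, where nurses did not invite all eligible patients. This has some force: a fuller protocol may contain the safeguard. But the article fixes a household rule for one route and an all-inclusive invitation for the other, so the point rests on what is stated.

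Objections to the size largely stand. Apart from the 31%, the inputs to the exposed share are assumed, and the 31% is a general-population figure that ignores the language, internet and computer-skill criteria. A joining probability of 80% sits badly with a pilot in which many patients declined. Full spill-over ignores personal accounts, individually tailored feedback and the non-use that the Discussion expects.

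A reader might infer that a control partner is directly exposed because the social influence component mentions partners. The text does not support this: the assessment and feedback go to the participant, so exposure of the partner is indirect. A reader might also infer that both primary comparisons are materially weakened. For physical activity they are not (step 6). Separate analysis of the practice stratum is conditional, and its precision would then depend mainly on its size.

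**Conclusion.** The gap is real but minor. As written, the plan lets co-resident practice patients fall in opposite arms, which the sponsor's own rule prevents within the panel. The direction of the bias is clear, towards no effect in the practice stratum, but its frequency is unknown because the article gives neither the practice share nor the number of couples.

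In the central assumed case whole-trial power for smoking drops by about 1.4 points and stays above 80%. It falls below 80% only when every assumption is set at its extreme and spill-over is complete, and the 49.2% smoking discount alone then brings it back to 80% or slightly above. The documents do not support a claim that the trial is underpowered for this reason.

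**What to change.** Apply the panel's rule to the practice mailing lists: where several eligible patients share an address, select one at random and invite only that person. This must be done before randomisation, because exposure cannot be undone in the analysis. The calculation behind 446 per arm does not change.

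The work is an address check before mailing. The price is a smaller practice stratum, which the panel cannot be assumed to refill because all its active members aged 40 to 70 are already invited. In the central case:
- If one member of each co-enrolled couple is lost, the sample shrinks by 0.30 × 5.4% = 1.6%, from 219 to 215.4 smokers per arm. Power becomes 81.5% (Wald) or 83.0% (z-test), a loss of about 0.6 points.
- If the unselected partner is never invited, even when the selected one declines, the loss is half of all practice participants with an eligible partner: 0.7 × 0.31 / 2 = 10.9% of the stratum, or 3.3% of the sample (211.9 smokers per arm). Power becomes 80.9% or 82.4%, a loss of about 1.3 points.

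The rule therefore buys an unbiased comparison and independent observations, not extra power. Two further measures are optional. Allocating a household to one arm brings clustering and makes the second partner's arm predictable. Matching addresses across the two routes requires panel and practice address data to be linked.

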#### Sample size calculation

The sample size for smoking is based on the assumption that 49.2% of the population with an increased COPD risk smokes [22]. A sample size calculation by PS software [23] indicates that 446 participants will be necessary in each arm at the end of the trial to detect 20% 7-day point prevalence abstinence in the intervention group, compared to 10% in the control group [24], with a 80% power and a significance level of 0.05. Since we do not uphold an upper bound for minutes a person can be physically active, 100% of the participants will be included in the analyses for physical activity. In another study the standard deviation for the Dutch population was 26.63 [25]. Considering this, we will need 112 participants in each arm, which is feasible to obtain from the suggested sample of 446 participants in order to detect a difference of 10 minutes with 80% power and a 0.05 significance level.

#### Randomisation

Participants will be randomly allocated to intervention and control groups after filling out the baseline questionnaire. Randomization will be stratified by method of recruitment (online or through general practice) and participants are randomised within each stratum using a permuted block design with a random block size varying from 4 to 20. This approach helps us achieve balanced and evenly distributed samples in both groups following different recruitment strategies. A researcher who is not directly involved in other aspects of the study will perform the randomisation using PROC PLAN in Statistical Analysis System v9.1 software (SAS Institute, Cary, NC). Figure 1 shows an overview of the recruitment and randomisation process.

**Figure 1 F1:**
[figure not shown]
Overview of the recruitment and randomisation of participants.

### Web-based intervention

#### Framework

The web-based intervention in this project was created with ‘Tailorbuilder’ software package (OverNite Software Europe B.V., The Netherlands), an internet application based on Perl and a MySQL5 database, which includes web-based questionnaires to identify user characteristics, a database with feedback messages and an algorithm with routing procedures and tailoring rules (algorithm). Feedback messages are derived from participants’ answers. Responses are linked to relevant messages [9]. Message selection and linking occurs by means of routing procedures and tailoring rules using principles of previously designed computer-tailored studies [11,26]. Messages are displayed after participants have filled out the questionnaire. The web-based intervention consists of two behaviour change modules, including smoking cessation and physical activity.

#### Behaviour change modules

The web-based intervention is based on modules developed in earlier studies targeting smoking cessation and physical activity for the general population [11,27]. We adapted these modules for COPD patients and for people at risk for COPD. We used the I-Change model as theoretical framework in our intervention [28]. This model includes several health promotion theories, i.e.: the Attitude-Social influence-Self-efficacy model (ASE) [29], which can be thought of as an incorporation of ideas of the Theory of Planned Behavior [30], the Social Cognitive Theory [31], the Transtheoretical Model [32], the Health Belief Model [33], and Implementation and Goal setting theories [31,34,35]. We evaluated and improved the usability of the behaviour change modules in a previous study [20].

The smoking cessation and physical activity modules provide participants with tailored feedback messages. Tailoring algorithms consider demographical characteristics and psychosocial constructs to generate personalized messages. The questionnaires have been tested experimentally among Dutch adults in previous studies [16,36,37]. The messages consist of texts, graphs and illustrations. Smoking cessation and physical activity modules include each the 6 intervention components described below.

1) The health risk appraisal

The health risk appraisal measures the behaviour (smoking and physical activity) and provides feedback based on Dutch guidelines for health behaviour. The feedback contains an explanation of how participants’ behaviour compares to the level of compliance with the Dutch guidelines. This is illustrated with a traffic light system, where a green light refers to meeting recommendations, a yellow light to partly meeting the recommendations and a red traffic light indicating lack of compliance with the recommendations [38]. The behavioural feedback can be tracked each time participants complete the health risk appraisal and ipsative feedback [39] will be offered regarding changes in behaviour over time. At last, a graph that shows specific behaviour changes over time is presented.

2) Motivational beliefs

The attitude toward a relevant behaviour is assessed and the perceived positive (e.g. health benefit) and negative consequences (e.g. weight gain for non-smoking) of the behaviour are addressed to confirm, correct or place participants’ beliefs in perspective.

3) Social influence

Social influences of participants’ partner, family, friends and co-workers on the specific behaviour are assessed. An explanation about how these influence the behaviour of the participants and how the participants influence others is provided. Information about how to cope with social pressure, the importance of social support and being or noticing a good role model is emphasized.

4) Goal setting and action plans

Participants can set a goal for behaviour change. They will be guided through questions to formulate the goal (e.g. starting next week I want to be physically active for 20 minutes a day, 3 times a week). Hereafter, they can choose from a list of action plans to achieve their goal and receive feedback with additional advice on how to increase the likelihood for their plans to succeed. One week after the goal is due, participants will receive an e-mail prompt to revisit this intervention component and indicate whether they achieved their goal, receive feedback and have the opportunity to adjust their goal and make new action plans.

5) Self efficacy

Barriers to perform the healthy behaviour are assessed, by asking participants which situations they find difficult. Moreover, participants are asked to indicate whether they have made plans to overcome these difficult situations (coping plans). Consequently, participants receive a list of the situations that they indicated to be difficult and are encouraged to follow through with their plans. Suggestions for plans are given if they had not already made a plan.

6) Maintenance

This component is similar to self-efficacy, but focuses on maintaining instead of changing the behaviour.

